#### Experimental condition: perceived social support and self-efficacy enhancement modules (enabling hypothesis)

This experimental condition reflects the enabling hypothesis and consists of the same modules as the first experimental condition (cultivation hypothesis) but in reverse order. Participants will first be presented with exercises comprising the SS module, and then the SE module. Participation in this condition also lasts 6 weeks with each exercise being released at the beginning of every week. Similarly, as in the previous condition, participants can optionally engage in one or more out of four additional modules: relaxation, mindfulness, cognitive restructuring, and lifestyle.

#### Active control condition: self-efficacy enhancement module

In this active control condition participants will only be presented with the SE module comprising the same three evidence-based, CBT-framed exercises as in the experimental conditions. Participants will also have access to the same four optional modules. This condition only takes 3 weeks, with one exercise being released each week.

#### Active control condition: social support enhancement module

In the second active control condition participants will only be presented with the SS module comprising the same three evidence-based, CBT-framed exercises as in the experimental conditions. Here again, participants will have access to four optional modules. This condition lasts 3 weeks, with one exercise being released each week.

#### Optional modules

##### Relaxation

This module consists of four voice-guided exercises: (1) breathing, (2) progressive relaxation, (3) visualizing the body’s warmth and weight, and (4) visualizing a calm place. The module aims to provide tools for active relaxation and helps to decrease muscular tension and strain. Participants will be free to do any number of these exercises at any time during the intervention.

##### Mindfulness

This module consists of four voice-guided or text-guided exercises: (1) how do body and mind react to thoughts? (2) body scanning, (3) breathing and sounds, and (4) being mindful of emotions. All exercises are designed to strengthen attention, body, thoughts, and emotional awareness to reduce perceived stress. Again, participants can do any chosen number of these exercises throughout the intervention.

##### Cognitive restructuring

Three exercises constitute this module: (1) opinion or fact, (2) identifying thinking traps, and (3) how important will this be in the future? This module provides an insight into the CBT technique of identifying and altering stress-inducing thoughts. Participants can choose one exercise or do all of them at any point during the intervention.

##### Lifestyle

This module consists of two exercises: (1) physical activity and (2) pleasant activities, which encourage participants to plan and implement activities fostering stress reduction. Users can do only one or both of these exercises throughout the intervention.

### Platform

The Med-Stress intervention was built on the Iterapi Internet platform [46], developed and administered at Linköping University in Sweden. The platform is widely used for international research on psychological Internet-based interventions. It provides professional software, secure transfer (https protocol), and data collection and storage protection required by local and European Union (EU) law, including General Data Protection Regulation (GDPR) (EU/2016/679). All data collected during the intervention and accompanying assessments, including the participants’ consent will be entered directly on the platform by participants and automatically encrypted, coded, and stored on the Iterapi server. Data stored will be depersonalized and masked, with access for authorized persons only.

### Randomization and blinding

Randomization will be carried out using an online randomization program (randomizer.org). Non-stratified block randomization with a 1:1:1:1 allocation ratio will be used to ensure an equal number of participants in all four study conditions (fixed blocks of 4). Participants will not be informed about the condition to which they are assigned, however they will not be blinded to their allocation, as it is publicly known that this intervention consists of four alternatives that differ in duration.

### Outcomes

#### Primary outcomes

There will be two primary outcomes in this study: job stress and job burnout.

The Perceived Stress Scale 14 (PSS-14) [2] will be used to measure job stress. We adapted the questionnaire’s instruction to refer to occupational stress. It consists of 14 items with the response scale ranging from 0 (never) to 4 (very often). A higher total score represents higher perceived stress.

The Oldenburg Burnout Inventory (OLBI) [47] will be applied to measure job burnout. It consists of 16 items with the response scale ranging from 1 (strongly agree) to 4 (strongly disagree). The questionnaire consists of two subscales: exhaustion and disengagement. A higher total score represents greater job burnout.

#### Secondary outcomes

Secondary outcome measures in this study include depression, work engagement and job-related traumatic stress.

The Patient Health Questionnaire (PHQ-9) [48] will be used to measure depression. This scale consists of 9 items and the responses range from 0 (not at all) to 3 (nearly every day). A higher total score represents greater depression.

The Utrecht Work Engagement Scale (UWES-3) [49] will be used to measure work engagement. It is the ultra-short version of the scale, which consists of 3 items and the response scale ranges from 0 (never) to 6 (always). A higher total score represents greater work engagement.

The Posttraumatic Stress Disorder Checklist 5 (PCL-5) [50] will be applied to measure traumatic stress symptoms. The questionnaire consists of four subscales: intrusions, avoidance, negative alterations in cognition and mood, and arousal. The response scale for 20 items range from 0 (not at all) to 4 (extremely). A higher total score represents higher traumatic stress. We adapted the instruction to refer to job-related indirect trauma exposure.

#### Other measures

Additionally, in this study we will measure self-efficacy to manage job burnout and work stress, social support self-efficacy, perceived social support, secondary trauma exposure, and initial expectancy of improvement and perceived credibility of the intervention.

The Work Stress and Job Burnout Self-Efficacy Scale (WSBSES) [51] will be used to measure the first type of self-efficacy. It consists of 28 items with the response scale ranging from 1 (I am definitely not capable) to 7 (I am definitely capable). A higher total score represents greater self-efficacy.

The Berlin Social Support Scales, Subscale 3 (BSSS) [52] will measure social support self-efficacy. The scale was originally designed to measure social support but we adapted its instruction and response scale to reflect self-efficacy for obtaining social support. The scale comprises 5 items and the revised response scale ranges from 1 (I am definitely not capable) to 7 (I am definitely capable). A higher total score represents greater social support self-efficacy.

The Who Can You Count On Scale [53] will measure perceived social support. It consists of 32 items with the response scale ranging from 1 (to very little extent) to 5 (to great extent). The questionnaire consists of 4 subscales: support form supervisors, support from coworkers, support from friends, and support from family. A higher total score represents greater perceived social support.

The Secondary Trauma Exposure Scale (STES) [54] will be used to measure job-related indirect exposure to traumatic events. The scale consists of 13 items with a yes/no response scale for 10 items, 2 items with a response scale ranging from 1 (none/never) to 7 (a few thousands/every day), and one item from 0% to 100%. A higher total score represents greater indirect exposure. Additionally, we will assess direct exposure to traumatic events with a single question on the number of events listed in the STES (response scale from 0 to 10).

The Credibility and Expectancy Questionnaire (CEQ) [55] will be applied to measure users’ expectancy and credibility of the intervention. This scale consists of 6 items, with a response scale for 4 items ranging from 1 (not at all) to 9 (very), and for the remaining 2 items from 0% to 100%. A higher total score represents higher treatment credibility and the user’s expectancy of improvement.

All the scales will be measured pretest, posttest, and at the two follow ups (at 6 and 12 months). The exceptions are STES and CEQ, which will only be assessed at baseline. All scales included have been validated in Poland and their reliability was tested in a feasibility study with satisfying results, with Cronbach’s alpha between 0.75 and 0.97. Completion of the surveys takes about 20 min.

### Statistical analysis

We will conduct analyses of covariance (ANCOVA) with condition assignment as a factor, all primary and secondary measures at posttest as outcomes, and their pretest values as covariates. This will allow us to test for group differences between study conditions posttest while controlling for change over time. ANCOVA has been shown to be more parsimonious than analysis of variance (ANOVA) in randomized trials with a repeated measures design, and thus to have more power [56]. In terms of specific analyses, primarily, we will compare the effects of experimental conditions to each active control to test whether a two-module intervention is more effective that a single-module one. Next, we will compare the effects of the two experimental conditions to check if the sequence of the modules contributes to the intervention effects. Bonferroni’s adjustment for multiple comparisons (five comparisons and five outcomes) will be applied, which will lower the *p* levels to .002 for detection of the effects. Additionally, we will conduct separate ANCOVA to test whether the differences in outcomes between study conditions are maintained at the 6-month and 12-month follow up. Furthermore, we will conduct mediation analyses to verify the hypothesized mechanism of the effect of condition assignment on the primary and secondary outcomes. Sequential mediation analyses will be applied using the PROCESS macro [57] with condition assignment as a predictor, primary and secondary measures posttest as the outcomes, their baseline scores as covariates, and self-efficacy and perceived social support posttest as mediators (see Figs. 1 and 2 for conceptual models of mediations).

Additionally, we will carry out moderation analysis to test whether the initial (pre-intervention) expectancy about the positive outcomes of the treatment (i.e., how successful the intervention would be in reducing stress and burnout symptoms in participants’ opinions) moderates the relationship between the condition assignment and the study outcomes. As participants in the study will have the option of engaging in one or more out of four additional modules, we will consider participation in them as a control variable.

Analyses will be conducted on the intention-to-treat (ITT) sample: all randomized participants will be included in the analyses regardless of their adherence and completion of the intervention. Per-protocol analyses in the sample of those participants who provide responses posttest will additionally be performed. Results of ITT and per-protocol analyses will be compared to check the robustness of the effects. Range and randomness of the missing data will be assessed with Little’s missing completely at random test [58]. Furthermore, we will conduct a dropout analysis comparing the baseline scores of those participants that remained in the study and those that dropped out, using ANOVA for continuous variables and χ^*2*^ tests for categorical variables. Dropout will be defined as those participants who did not fill out measurements beyond pretest. Missing data will be imputed by the means of multiple imputation. Because study outcomes are assessed three times, we will impute missing data using the baseline measurements as predictors, the measurements of the subsequent outcomes and the baseline covariates that could potentially be responsible for the missing data [59].

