Workplace interventions usually take into account the specific environmental factors, which maximizes the fit with their receivers’ needs but makes them difficult or impossible to generalize. An alternative is intervention targeting individual and social resources. The obvious downside of such interventions is that they do not match the needs exactly, but on the upside, have a greater chance of being relevant to many employees across a variety of workplaces. In other words, resource-based interventions can be beneficial for more employees, but might not address all their issues. According to conservation of resources theory [20], resources are “those objects, personal characteristics, conditions, or energies that are valued in their own rights, or that are valued because they act as conduits to the achievement or protection of valued resources” (p. 339). In this study we will consider two psychological resources, self-efficacy and perceived social support, the conduits to prevent and manage job stress and burnout, as well as expect their role in increasing work engagement, and decreasing depression and job-related traumatic stress.

Self-efficacy, a crucial concept in social cognitive theory [30], determines how people feel, think, and behave, and reflects their belief in being able to perform competently and achieve set goals despite obstacles. It allows the prediction of how employees will cope with work stress [31] and was found to have a medium, negative relationship with job burnout [32]. Apart from general self-efficacy, we distinguish context- or domain-specific self-efficacy, which is considered better at explaining and predicting outcomes [33]. As the primary outcomes in this study are job stress and burnout, we are interested in self-efficacy to cope with those. Additionally, as we explain later in this paper, we focus on the relationship between self-efficacy and perceived social support, and thus introduce self-efficacy to obtain social support.

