**Fig. 4 Fig4:**
[figure not shown]
Schedule of enrolment, interventions, and assessments

Participants will be recruited via targeted Facebook ads, the project’s website and through promotion in the regional and national media. Interested participants will be invited to visit the intervention public page (medstres.pl) and watch a short video clip in which the project’s team explains the purpose and scope of the study. Subsequently, they will be asked to declare whether they are at least 18 years old, represent medical professions, and have access to an Internet-connected device; all in order to check whether they are eligible to participate. Upon registration, participants will be asked to provide informed consent. All registration procedures will be conducted online, with no contact from the research team. The implications of participation in the study will be clearly explained in the materials (text and a video clip) on the public website and in the informed consent document. This process was approved by the research ethics committee. After accepting to be randomized to one of four study conditions, participants will be asked to fill out the baseline questionnaires (pretest). Once those are completed, participants will be randomized and allocated with a 1:1:1:1 ratio to one of four study conditions. The registration process is continuous, which means that access to the Med-Stress program is given instantly, but the content is released on Mondays. Every week a new exercise is available and participants will be notified via e-mail. Such a recurrent design is determined by the task that requires participants in three conditions (those that include a perceived social support enhancement module) to take part in a forum discussion at the same time. Depending on the study condition, the intervention will take 3 weeks (active control conditions) or 6 weeks (experimental conditions). Participants will not be informed about the result of the allocation but it is public knowledge that Med-Stress consists of four variants that differ in terms of length (depending on whether a given variant contains one or two modules) and the type of exercises. Regardless of the condition, all participants have access to four optional modules throughout the study: Relaxation, Mindfulness, Cognitive Restructuring, and Lifestyle. Participants will be asked to fill out questionnaires at four times during the study: before the intervention, posttest (i.e., right after the intervention: at 3 or 6 weeks depending on the study condition), and at 6-month and 12-month follow up. Additionally, users assigned to experimental conditions will undergo mid-intervention assessment. Depending on the first module, perceived social support (one scale) or self-efficacy (two scales: self-efficacy to manage job stress and burnout, and self-efficacy to obtain social support) will be measured. At each assessment point, participants will receive an e-mail notification containing a link to the survey. All measurements throughout the study will be obtained online, which has been shown to be a reliable mode of administering psychological, self-report questionnaires [45]. To ensure a high response rate, each e-mail notification will be followed by two reminders every 2 days. Moreover, we will include supportive messages in the survey between questionnaires, thanking the participants for getting this far and encouraging them to continue until completion. All participants will be advised that should they experience any psychological discomfort, harm, or other unintended effects of the intervention or study, they are encouraged to contact the study team or other mental-health professionals. At any time during the intervention period and after completing the program, the participants have the right to withdraw their participation without the obligation to provide their reasons, as stated in the informed consent.

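### Each ANCOVA adjusts for one baseline scale, the outcome's own pretest, although ten are completed before randomisation; a fixed wider set could add some precision at almost no cost

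*Protocol article*

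**What the plan says.** - **Model.** The Statistical analysis section specifies ANCOVA with condition as the factor, "all primary and secondary measures at posttest as outcomes, and their pretest values as covariates". Separate ANCOVAs follow for 6 and 12 months. Five comparisons on five outcomes bring the significance level to .002.
- **Other adjustment.** The only further adjustment named there concerns use of the four optional modules: "we will consider participation in them as a control variable". The section does not say in which model.
- **What is measured.** Under Other measures: "All the scales will be measured pretest, posttest, and at the two follow ups". Then: "The exceptions are STES and CEQ, which will only be assessed at baseline". Counting through the Outcomes section, eight scales are repeated (PSS-14, OLBI, PHQ-9, UWES-3, PCL-5, WSBSES, the adapted BSSS subscale and the perceived support scale). STES and CEQ make ten at baseline.
- **Timing.** The Procedure section places the baseline questionnaires before allocation: "Once those are completed, participants will be randomized and allocated with a 1:1:1:1 ratio to one of four study conditions".
- **Expected relations.** The Background says that self-efficacy "was found to have a medium, negative relationship with job burnout", and reports a small negative relationship for perceived support.
- **Missing data.** The multiple imputation already draws on baseline measurements and on baseline covariates that may explain missingness. An additional analysis is restricted to those who respond at posttest, is called per-protocol, and is compared with the ITT result as a check of robustness.

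**The concern.** The word *their* most naturally pairs each posttest score with its own pretest. A single pretest measures a person's level with error: the feasibility study's Cronbach's alphas run from 0.75 to 0.97. Related pretests may carry prognostic information that the outcome's own pretest misses. Because randomisation follows the completed pretest, these scores should be available for everyone randomised.

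Two things are at stake. First, precision: any outcome variance that the other pretests could explain stays in the error term of all 25 posttest tests, each judged at .002. Second, the robustness comparison: the imputed ITT analysis uses broad baseline information, while the responder ANCOVA uses one baseline score. If the two disagree, the difference in covariates is one possible reason, and it could be removed in advance. With cited dropout of 5 to 45%, that comparison may matter.

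**Working it through.** **1. The plan's own figures.** The level is 0.05/(5 × 5) = 0.002, as stated. The evaluable N of 607 reproduces exactly as an omnibus F test of four groups (numerator df 3, noncentrality f² × N, f = 0.20, alpha 0.002, power 0.90). It is 607 whether 0, 1, 5 or 8 covariates are counted, so the number of covariates does not affect the planned size. The text labels the effect d = 0.20; for a two-group comparison at d = 0.20 the same level and power need 956 per arm without a covariate. That is a separate and larger matter.

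**2. Inputs for the gain.** The protocol gives no correlations, so all three of these are assumptions:
- o, own pretest with posttest: 0.5 or 0.6
- c, each of two related pretests with posttest: 0.35, 0.40 or 0.45
- ρ, correlation among the three pretests: 0.4, 0.5 or 0.6

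**3. Formula.** With own pretest alone, R² = o². Adding two related pretests raises it by

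(2c − 2ρo)² / (2 + 2ρ − 4ρ²).

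The proportional fall in residual variance is q = increase / (1 − o²). The equivalent number of extra participants is 1200 × (1/(1 − q) − 1).

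**4. Results: fall in residual variance, q**

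| ρ | o | c = 0.35 | c = 0.40 | c = 0.45 |
|---|---|---|---|---|
| 0.4 | 0.5 | 5.6% | 9.9% | 15.4% |
| 0.5 | 0.5 | 2.7% | 6.0% | 10.7% |
| 0.6 | 0.5 | 0.8% | 3.0% | 6.8% |
| 0.4 | 0.6 | 3.5% | 7.4% | 12.8% |
| 0.5 | 0.6 | 0.8% | 3.1% | 7.0% |
| 0.6 | 0.6 | 0.04% | 0.6% | 2.9% |

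- Smallest: (0.70 − 0.72)²/1.76 = 0.0002, so R² is 0.3602 against 0.36. That equals 0.4 of a participant.
- Largest: (0.90 − 0.40)²/2.16 = 0.1157, so q = 0.1157/0.75 = 15.4%. That equals 219 participants.
- Nine of the 18 combinations give 3.5% or less.

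**5. In terms of power.** For a pairwise test at d = 0.20, alpha 0.002 two-sided and 300 per arm, power is 0.261 with no covariate. Own pretest alone gives 0.397 at o = 0.5 and 0.489 at o = 0.6. With the two related pretests added, the grid gives 0.401 to 0.494 at o = 0.5 and 0.489 to 0.575 at o = 0.6. In most of the grid the own pretest supplies most of the gain.

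**6. Cost if the extra scales explain nothing.** Seven added covariates reduce the residual degrees of freedom from 1195 to 1188 at N = 1200, a ratio of 1.006. At N = 608 (4 × 152) they fall from 603 to 596, a ratio of 1.012. The penalty is therefore about 0.6 to 1.2% of residual variance.

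**7. Limit of the calculation.** It models two added pretests; the proposed set adds seven. Without correlations, the gain from the full set cannot be stated.

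**The case against.** The strongest reply is that nothing here is wrong. An ANCOVA on the outcome's own pretest is valid and unbiased in a randomised trial, the protocol chooses it for a stated reason (more power than ANOVA), and further covariates are often left to an analysis plan, which is not shown. All of this stands, and it makes the point an optional improvement. What remains is that the protocol does name its covariates, and the set it names is narrower than its data allow.

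A second reply is that the Background reports plain correlations with burnout, whereas what counts is prediction of the posttest beyond its own pretest. This also stands, and it is why the range begins at zero.

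Some stronger readings are tempting but unsupported:
- *That a definite gain is forfeited.* The assumed ranges include essentially none.
- *That no other adjustment is planned.* Optional-module use is named as a control variable. It arises after randomisation, so it is not a baseline covariate and cannot supply baseline precision.
- *That the imputation ignores these scales.* The missing-data text already provides for baseline measurements and covariates, so dropout in the main ITT analysis is largely addressed. The gap concerns only the responder analysis.
- *That entry date should be in the model.* The protocol specifies "Non-stratified block randomization with a 1:1:1:1 allocation ratio" in fixed blocks of four. There is no stratification factor to adjust for, the blocks already balance the arms over entry order, and no time trend is documented.

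**Conclusion.** The point holds as a minor efficiency improvement. On the natural reading, the outcome's own pretest is the only baseline covariate in each ANCOVA, although ten scales precede randomisation. Under the assumed correlations, two related pretests would lower residual variance by about 0 to 15%, with low single digits plausible; the true figure is unknown because the protocol gives no correlations. The planned analysis remains valid and unbiased without the change. A shared covariate set would also make the responder analysis more comparable with the imputed one.

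A reader might infer that wider adjustment would rescue power at .002. It would not: even at the favourable end of the grid, power for a pairwise difference of d = 0.20 with 300 per arm stays at 0.575, well below the planned 0.90.

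**What to change.** In the Statistical analysis section, prespecify one baseline covariate set for the ANCOVAs at posttest, 6 months and 12 months:
- the outcome's own pretest;
- the pretests of the other four outcomes;
- the pretests of the two self-efficacy scales (WSBSES and the adapted BSSS subscale) and of perceived social support.

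State that the posttest-responder analysis uses the same set, so that it conditions on the same baseline information as the imputation already planned. Fixing the list in advance also prevents a later choice among ten baseline scales.

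The cost is one sentence, no new data and about seven degrees of freedom. In a linear model the treatment contrast being estimated is unchanged. If the added scales explain nothing, the loss is the 0.6 to 1.2% of residual variance shown above.

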To summarize, the goal of this study is to test the efficacy of an internet-based intervention, Med-Stress, targeted mainly at reducing job stress and burnout among medical professionals, through the individual and sequential enhancement of self-efficacy and perceived social support. Med-Stress comprises two main modules - one dedicated to self-efficacy, and the other to perceived social support - that are then tested in four configurations that translate into four study conditions. Both modules are included in two of these conditions, which means that the resources are strengthened sequentially: in the first variant, a self-efficacy enhancement module precedes a perceived social support enhancement module, whereas in the second variant the order is reversed. Throughout the protocol we refer to these study conditions as experimental ones. Only one module is included in the remaining two conditions, which means that a single resource is targeted; either self-efficacy or perceived social support. These conditions are referred to as active controls. We expect that participation in all conditions will lead to significant changes in primary and secondary outcomes from the baseline to posttest. However, a greater decrease in job stress and job burnout (primary outcomes), depression, and traumatic stress symptoms, and greater increase in work engagement (secondary outcomes) at the posttest will be observed among the participants in the experimental conditions than among those in active control conditions. These differences will be maintained at the 6-month and 12-month follow up.

At the same time, we see no theoretical or empirical grounds to predict which of the two experimental conditions will be more effective than the other in reducing stress and burnout, and thus we consider a comparison between cultivation and enabling effects an explorative part of the study (see Figs. 1 and 2).

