### Sample size

The study will be conducted among professionally active health professionals at risk of job stress and burnout. Bonferroni’s adjustment for multiple comparisons will be applied: there will be a comparison between the two experimental conditions and between each experimental condition and each active control condition giving a total of five comparisons posttest. Furthermore, we will include five outcomes. Taken together, this will lower *p* levels to .002. Meta-analyses of the effectiveness of web-based interventions for stress reduction found a small effect of *g* = 0.30 [19] for work-related stress, and a medium size effect of *d* = 0.49 for general stress [43]. Taking into account the minimum effect size of *d* = 0.20, in analysis of covariance (ANCOVA) with a significance level of α = 0.002, statistical power of 0.90, and the number of conditions (two experimental conditions and two active controls), a total of 607 participants will be set (152 participants per condition). Furthermore, a high dropout rate is usually encountered in unguided interventions (between 5 and 45%; [44]) and thus we ultimately plan for a sample of 1200 participants (300 participants per condition).

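### A flat 25-test Bonferroni family at 0.002 is valid for posttest but needlessly strict for the two primary outcomes, and it does not cover the 6- and 12-month tests

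*Protocol article*

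**What the plan says.** The Sample size section of the protocol article sets up the family. It states that "there will be a comparison between the two experimental conditions and between each experimental condition and each active control condition", and counts these as five at posttest. It then adds: "Furthermore, we will include five outcomes". The trial is sized "with a significance level of α = 0.002, statistical power of 0.90". The Statistical analysis section repeats the rule: Bonferroni's "adjustment for multiple comparisons (five comparisons and five outcomes) will be applied".

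Three other statements bear on this:

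- The Background says of the two experimental conditions that "we consider a comparison between cultivation and enabling effects an explorative part of the study". The Statistical analysis section also places that comparison second, after the comparisons of experimental conditions with active controls.
- The Outcomes section names two primary outcomes (job stress on the PSS-14, job burnout on the OLBI) and three secondary ones (depression, work engagement, job-related traumatic stress).
- After the adjustment sentence, the Statistical analysis section adds that "we will conduct separate ANCOVA to test whether the differences in outcomes between study conditions are maintained" at 6 and 12 months. No significance level is attached to those tests. The Background and the Discussion both state maintenance as an expected result.

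**The concern.** The plan ranks its questions but does not test them by rank. It names primary outcomes, puts the experimental-versus-control comparisons first and calls the sequence comparison explorative. All 25 posttest tests then receive the same single-step threshold, so being primary gives an outcome no priority. The four comparisons on two primary outcomes make 8 tests. They are judged at 0.002, although a family of their own would start at 0.05/8 = 0.00625.

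The opposite problem arises at follow-up. The family is counted at posttest only, yet the article makes a directional prediction about 6 and 12 months. A statement that differences were maintained would fall outside the error control that the article describes.

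At stake are the chance of answering the main question at the smallest effect the plan names, and the standing of the long-term claims.

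**Working it through.** **1. The plan's own figures.** 5 comparisons × 5 outcomes = 25, and 0.05/25 = 0.002, as stated. The 607 participants reproduce with a noncentral F test: 4 groups, 1 covariate, 3 numerator df, noncentrality f²N with f = 0.20, level 0.002, power 0.90. This gives N = 607 (power 0.9002). The article labels 0.20 as d, but 607 comes out only when it is read as Cohen's f in the omnibus test. That is a separate matter, used here only to reproduce the figure.

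**2. Where the cost lies, on those same omnibus inputs.**

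| Family | Tests | Level | N for 90% power | Power at N = 607 |
|---|---|---|---|---|
| As planned | 25 | 0.002 | 607 | 0.900 |
| Drop the explorative comparison only | 20 | 0.0025 | 591 | 0.911 |
| Drop the secondary outcomes only | 10 | 0.005 | 540 | 0.940 |
| Drop both | 8 | 0.00625 | 523 | 0.948 |

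The explorative comparison costs 607 − 591 = 16 participants. The secondary outcomes cost 607 − 540 = 67. Together the saving is (607 − 523)/607 = 14%.

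**3. The pairwise tests the plan will actually run.** For one two-sided contrast with n per arm and pre-post correlation r, single-step power is about Φ(d√(n/2)/√(1 − r²) − z), where z is the critical value: 3.090 at 0.002 and 2.734 at 0.00625. Take d = 0.20 (the plan's minimum), n = 300 (the planned arm size, no dropout) and r = 0:

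- 0.20 × √150 = 2.449
- At 0.002: Φ(2.449 − 3.090) = 0.26
- At 0.00625: Φ(2.449 − 2.734) = 0.39

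Holm depends on the other tests in the family, so it was simulated (20,000 trials per setting). Assumptions: both experimental arms better than both controls by d on all five outcomes, outcomes correlated 0.5. The entries are average power per primary test.

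| n per arm | d | r | Bonferroni-25 | Holm-25 | Holm-8 |
|---|---|---|---|---|---|
| 300 | 0.20 | 0 | 0.26 | 0.30 | 0.48 |
| 300 | 0.20 | 0.6 | 0.49 | 0.56 | 0.75 |
| 165 | 0.20 | 0.6 | 0.21 | 0.23 | 0.39 |
| 165 | 0.30 | 0.6 | 0.62 | 0.70 | 0.86 |

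The 165 per arm is 300 × 0.55, the top of the article's 5 to 45% dropout range.

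**4. Follow-up.** The maintenance hypothesis in the Background concerns experimental versus control only: 4 comparisons × 5 outcomes × 2 times = 40 tests. Of these, 4 × 2 × 2 = 16 are on the primary outcomes. If all five comparisons were run there would be 50, and 25 + 50 = 75 over all time points. If 0.002 were carried over, the Bonferroni bound is 75 × 0.002 = 0.15, not 0.05. If 0.05 were used per test and every null were true, the expected number of false positives would be 40 × 0.05 = 2.0, or 16 × 0.05 = 0.8 for the primary outcomes. The article states neither level, so both are scenarios.

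**The case against.** The strongest defence is that nothing here is miscalculated. Bonferroni at 0.002 controls the 25 posttest tests, the trial was sized at that level, and on the plan's omnibus inputs the smaller family gains only about five power points. A single family also lets a secondary outcome be claimed in its own right, which gatekeeping gives up. Adjusting for an explorative comparison is cautious, and the article never calls it confirmatory. All of this stands. A reader might infer that the level is an error, or that the explorative comparison is what drains the power. The documents support neither: the level is valid, and that comparison alone moves N by 16.

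A reader might also infer that the maintenance claims are tested at 0.05 without any control, with 50 tests and 2.5 false positives expected. The article does not say so. It gives no level, the full protocol or an analysis plan may do so, and the hypothesis as worded covers 40 tests. What stands is narrower: the family as counted ends at posttest, and reusing its level would not hold overall error at 0.05.

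The power figures rest on correlations that are not in the documents, and 165 per arm is the worst dropout case. That is why r = 0 and full retention are shown as well. Part of the Holm-8 gain comes from Holm and part from the smaller family: at r = 0, n = 300 and d = 0.20, single-step 0.05/8 gives 0.39 and Holm-8 gives 0.48. Equal effects on all outcomes favour Holm. The low power at d = 0.20 also largely reflects the effect size itself, and no choice of family fully repairs it.

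**Conclusion.** The point holds as one of efficiency and scope. The 0.002 rule is valid for posttest but stricter than the plan's own ranking of its questions requires. For the pairwise primary tests at d = 0.20 and 300 per arm, moving to Holm over 8 raises average power from 0.26 to 0.48 (r = 0) or from 0.49 to 0.75 (r = 0.6), assuming outcome correlation 0.5 and equal effects on all outcomes. On the omnibus inputs, moving to single-step 0.05/8 raises power from 0.90 to 0.95. Most of the loss comes from putting three secondary outcomes in the same family as the primaries.

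Separately, the 25-test count does not extend to the 6- and 12-month tests that support the maintenance hypothesis, and the article states no level for them. The change is worth making because it needs no extra participants or data.

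**What to change.** At minimum, replace single-step Bonferroni by Holm over the same 25 posttest tests. Familywise error stays at 0.05, no test loses power, and the first step is still 0.002, so the sample-size level can stay.

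Preferably:

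1. Define the confirmatory family as the four experimental-versus-control comparisons on the PSS-14 and OLBI at posttest, tested by Holm at overall 0.05.
2. Keep experimental versus experimental outside the family, as explorative.
3. Test secondary outcomes and the 6- and 12-month contrasts only after the corresponding primary result is significant, or label them exploratory. If they are gated, state the level passed on to them.

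The cost is wording in the Statistical analysis section and a matching update of the level in the Sample size section, where 0.002 is an input. The real downside is that secondary outcomes can be formally claimed only after the primaries.
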